#### Intervention Format, Structure, and Content

Both SM and CM interventions last 15 months and involve Intensive Treatment and Maintenance phases.

#### Intensive Treatment Phase

The Intensive Treatment of both interventions lasts three months and is based on the GLB program [13]. There are 12 weekly sessions and each lasts 90-120 minutes. Each session follows a similar structure and includes five curriculum components: 1) measurement and recording of weight, 2) review of self-monitoring records and progress, 3) identification of personal barriers to weight loss and activity and potential solutions, 4) presentation of a new content area, and 5) goal setting and action plans for next week.

SM condition. After attending a single-session group orientation, participants in the SM intervention are given the GLB program on a DVD to follow at home, with access to a study dietitian via secure online messaging for advice and support. Secure messaging is integrated with the electronic health record and allows patients to communicate confidentially with their provider online. The DVDs are provided by the Diabetes Prevention Support Center at the University of Pittsburgh Diabetes Institute. Participants are encouraged to message the dietitian comments and questions as they are completing the DVD program. The dietitian will answer secure messages from participants within 1-2 work days and provide general support and encouragement.

CM condition. Participants in the CM intervention receive the GLB program in 12 weekly group sessions led by a study dietitian and exercise physiologist. Both interventionists have training and experience in weight management counseling, and the dietitian has completed the GLB 2-day training workshop offered by the University of Pittsburgh's Diabetes Prevention Support Center. The sessions are conducted in a highly interactive fashion. The GLB Manual of Operations is closely followed, except for the addition of a food tasting activity as part of the check-in process and a 30-minute physical activity demonstration at the end of each session. The food tasting activities are aimed at increasing participant experience with healthy food choices, encouraging them to try new foods that they might not normally try on their own, and stimulating a social, fun and engaging environment. The physical activity demonstrations are aimed at increasing participant awareness of physical activity intensity, experiencing various moderate-intensity activities that are safe and that they can easily incorporate into their daily lives, and increasing participant confidence. E-LITE participants in both CM and SM arms receive a pedometer in the initial session (the group orientation for the SM arm), as opposed to in session 10 as in the original GLB program [13].

#### Maintenance Phase

Both SM and CM interventions use secure online messaging as the primary mode of contact between participants and the dietitian during the maintenance phase. The contact time is likely to vary depending on individual needs in either intervention arm. The exercise physiologist is available to counsel the dietitian on issues related to physical activity but she will have no direct communication with participants in this phase. Participants are instructed to continue monitoring their weight, dietary intake, and physical activity at least twice each week.

SM condition. SM participants receive an email reminder every two weeks to continue self-monitoring. As in the Intensive Treatment phase, they are encouraged to submit comments and questions to the dietitian via secure messaging. The dietitian will respond to participant inquiries but will not initiate contact.

CM condition. In contrast, the dietitian provides active follow-up and individualized counseling to participants in the CM group via secure messaging on at least a monthly basis. Based on participant progress, the dietitian provides tailored feedback to reinforce progress, recommend problem solving and relapse prevention strategies, and encourage maintenance efforts. As the participant is successful or not in attaining his/her current goals, changes to the individual action plan are recommended, e.g., modifying goals, adding to them, or replacing them with new goals. The objective of any changes to the action plan is to keep the goals realistic yet challenging and to accommodate preferences and periodic fluctuations in motivation and schedule. Participants are encouraged to practice subject-initiated relapse prevention strategies, with feedback and support from the dietitian. Participants who fail to complete their self-monitoring diaries as scheduled are queried about their progress relative to their weight loss and behavioral change goals and any barriers they have encountered in attaining those goals. They are strongly encouraged to monitor and continue with the intervention. At the discretion of the dietitian, participants may be phoned or seen to address outstanding issues related to poor understanding of and/or adherence to the intervention protocol.

### Participant Safety

PCP approval is required before potentially eligible patients are contacted by the study. Participants are carefully screened and individuals for whom the interventions would be medically inappropriate or unsafe are excluded. During screening, women who are pregnant, lactating, or planning to become pregnant during the study period are excluded. If a participant becomes pregnant during the study, she is excluded immediately from further participation in all study activities, and her PCP is immediately notified. Participants who develop any other exclusionary condition (e.g., diabetes) following randomization may continue with the interventions and follow-up assessments only after explicit approval of their PCP. Surveillance for adverse events and relevant clinical events occurs by questionnaire at regularly scheduled intervals. Positive responses trigger an adverse event record, which is reviewed by the study physician for seriousness, study relatedness, and expectedness within 72 hours. Similar information reported by participants at other times (e.g., during intervention encounters) is duly noted and followed up with as needed to assure participant safety. Participants will be referred to their PCP for a medical evaluation and follow-up as needed or recommended by the study physician.

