**Exclusion criteria**
1. Inability to speak, read or understand English;
2. No regular access to a computer with Internet and email capabilities;
3. Triglycerides ≥ 400 mg/dL;
4. Systolic blood pressure ≥ 160 mm Hg or diastolic blood pressure ≥ 100 mm Hg;
5. Initiation or change of drug therapy for elevated blood pressure or abnormal lipid levels within the past 3 months;
6. Initiation or change of antidepressant medication within the past 3 months;
7. Having a medical or physical condition that make moderate intensity physical activity (like a brisk walk) difficult or unsafe;
8. Use of weight-loss medications in the past 3 months;
9. Regular use (> 5 days/month) of medications that affect appetite or weight (e.g., oral corticosteroids, insulin, oral hypoglycemics etc.);
10. Currently enrolled in a lifestyle intervention program at PAMF or elsewhere;
11. Planning to undergo bariatric surgery during the study period;
12. Diagnosis of Type 1 or Type 2 diabetes mellitus;
13. Significant medical co-morbidities, including uncontrolled metabolic disorders (e.g., thyroid, renal, liver), heart disease, stroke, and ongoing substance abuse;
14. Renal insufficiency (i.e. glomerular filtration rate < 60 mL/min/1.73 m^2^)
15. Diagnosis of psychiatric disorders that would limit adequate informed consent or ability to comply with study protocol;
16. Diagnosis of cancer (other than non-melanoma skin cancer) that was active or treated with radiation or chemotherapy within the past 2 years;
17. Diagnosis of a terminal illness and/or in hospice care;
18. Pregnant, lactating or planning to become pregnant during the study period;
19. Already enrolled or planning to enroll in a research study that would limit full participation in this study or confound the observation and interpretation of the study's findings;
20. Family/household member of another study participant or of a study staff member;
21. No longer a PAMF patient or planning to transfer care outside of PAMF during the study period;
22. Planning to move out of the area during the study period;
23. PCP determination that the study is medically inappropriate or unsafe for the patient;
24. Investigator discretion for clinical safety or protocol adherence reasons.

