### Data Analysis

The primary hypothesis compares BMI between each intervention (SM and CM) and usual care at 15 months using an intent-to-treat analysis. Linear mixed modeling,

using SAS PROC MIXED [54] will test time and group interactions to asses whether within-subject change in BMI differs by condition. This basic analytical strategy also accounts for the nature of repeated measurements, the blocked design by cohorts, and the clustering of patients within physicians. The same analysis strategy is appropriate for evaluating secondary aims where the hypotheses are identical but with different outcome measures (e.g., glycemic control, other component risk factors of the metabolic syndrome, and psychosocial well-being). The longitudinal effects of the interventions will be assessed using the same model, except that the focus is comparisons within intervention groups at different time points. Analyses will also be conducted to examine whether there is a dose-response relationship between intervention adherence and outcome, where dose is defined in terms of number of group sessions attended, number of secure messages sent, number of self-monitoring logs, average daily intakes of calories and fat, and average number of minutes of physical activity per week.

For participants with missing outcomes at the primary (15-month) or secondary (3- and 6-month) assessment point, we will conduct and report on sensitivity analyses in which different imputation methods are used (e.g., the baseline-observation-carried-forward method, the "hot deck" procedure, and an appropriate multiple imputation method [55,56].

We will use the MacArthur approach, which modified the Baron & Kenny criteria, for defining moderators and mediators in clinical research studies [57]. Let T be the treatment, M be the potential moderator or mediator, and O be the outcome. Association between T, M, and O is examined using the following models:(1)

M is a moderator of the effect of T on O if M precedes T, γ_1 _= 0, and β_3 _≠ 0. M is a mediator of the effect of T on O if T precedes M, γ_1 _≠ 0, and either β_2 _≠ 0 or β_3 _≠ 0.

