E-LITE is a randomized clinical trial aimed at rigorously evaluating the feasibility and potential effectiveness of translating two lifestyle interventions into ongoing care of overweight or obese adults with pre-diabetes and/or metabolic syndrome in a primary care practice. Studies of integrating the DPP lifestyle intervention to primary care settings are limited and few have used a randomized design [11,14,15]. In E-LITE, a DPP-based curriculum will be delivered in a self-guided DVD or in small groups, plus ongoing individual counseling via secure online messaging. Self-guided educational materials, group counseling, and secure messaging are modalities in use in contemporary health care systems. In addition to utilizing these potentially cost-effective means of delivering the intervention, the E-LITE study is designed and implemented with close attention to existing resources, skills, and barriers of the clinical setting in order to enhance its generalizability and sustainability. For example, we will recruit from an actual patient population in the clinic. We use data already available in the electronic health record to first identify an enriched pool of potentially eligible patients and then adopt a physician referral approach to promote safety and to facilitate integration of the intervention with primary care. Furthermore, we utilize well-trained non-physician clinicians (e.g., registered dietitians) who are already in the health care workforce to deliver the interventions, which will help address commonly cited barriers to primary care-based lifestyle programs in terms of physician time commitment and training. Finally, secure messaging is integrated with the electronic health record and all communications between the interventionist and the patient are viewable by the patient's PCP, which allows for integration of the intervention into ongoing care. Also, if proven successful, secure messaging would help address the need for ongoing, long-term support -- one of the greatest challenges of maintaining healthy lifestyles -- in primary care practice. With the advent of electronic health record systems and associated communication modalities, such population-based lifestyle interventions are a realistic possibility in the primary care setting.

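### PCP approval after a new exclusionary condition governs outcome assessment as well as treatment, so 15-month outcomes can be lost for outcome-related reasons; this weakens the intent-to-treat analysis but does not break it

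*Protocol article*

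**What the plan says.** Two rules in the Participant Safety section of the protocol article affect outcome collection after randomization.

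- **New exclusionary condition.** People who newly meet an exclusion criterion other than pregnancy once they are in the trial, with diabetes named as the example, "may continue with the interventions and follow-up assessments only after explicit approval of their PCP". The approval covers interventions and assessments together.
- **Pregnancy.** The participant leaves with no approval route: "she is excluded immediately from further participation in all study activities".

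The exclusion list in Table 1 shows what can trigger the first rule. Besides diabetes, it includes triglycerides of 400 mg/dL or more, blood pressure of 160/100 mm Hg or more, "Use of weight-loss medications in the past 3 months", and regular use of "medications that affect appetite or weight (e.g., oral corticosteroids, insulin, oral hypoglycemics etc".

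The Data Analysis section sets the estimand that these rules affect: "The primary hypothesis compares BMI between each intervention (SM and CM) and usual care at 15 months using an intent-to-treat analysis". It uses a linear mixed model on repeated measures. For missing outcomes, "we will conduct and report on sensitivity analyses in which different imputation methods are used"; the examples are baseline carried forward, hot deck and multiple imputation.

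The Retention section takes a different line. Staff try to re-engage people who miss an assessment, and they stay in touch with people who have stopped the intervention, partly so that these can still be recruited for the final assessment. It does not say whether this applies when a PCP has not given approval.

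**The concern.** An intent-to-treat comparison needs the outcome from everyone randomized, whether or not they stay on the intervention. Here a protocol rule can stop measurement after a health event that is related to the outcome. Fasting glucose and A1c are secondary outcomes, and the Background links obesity to diabetes. Several other triggers also follow weight and metabolic course.

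The trigger may also be related to arm. The trial hypothesizes smaller BMI reductions in usual care, which could mean more triggers there. On the other side, SM and CM participants have more study contact, which could mean more detection. The physician who decides may be able to tell that a patient is in an intervention arm, because "all communications between the interventionist and the patient are viewable by the patient's PCP". The blinding described under Randomization and Blinding covers investigators and staff responsible for follow-up data and analysis, not PCPs.

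At stake is avoidable informative missingness in the primary outcome. It would be sharper for glucose and A1c, where the triggering event can itself be a high value.

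**Working it through.** **1. The stated power reproduces.** Inputs from Sample Size and Randomization and Blinding: N = 240, allocation 1:1:1, 20% loss, effect 0.5 SD, two-sided alpha 0.05, t-test.

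- Per arm: 240 / 3 = 80; evaluable: 80 x (1 - 0.20) = 64.
- Two-sample t-test power at 64 per arm: 0.801, against the stated figure of about 80%.

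The sample size is not in dispute. If losses under the approval rule fall within the budgeted 20%, power is unchanged. If they come on top by 2, 5 or 10 percentage points, t-test power is 0.791, 0.775 or 0.746.

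**2. Steps needed for a loss.** A 15-month BMI is lost through this rule only if (a) an exclusionary condition develops, (b) it is detected before the 15-month assessment, and (c) the PCP refuses approval or does not give it. Table 2 schedules fasting bloods at 6 months and blood pressure at 3 and 6 months, so the trial's own visits can bring a trigger to light in time. Diabetes first found at month 15 costs no BMI value, because weight is measured at that same assessment.

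**3. Size of the bias.** The article gives no rate for (a), (b) or (c), so the following inputs are assumptions:

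- share lost this way: 5-15% in usual care, 3-8% in an intervention arm;
- gap between lost and retained participants: 0.5-1.0 SD worse, the same in both arms.

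For an available-case contrast, bias = (share lost in usual care - share lost in intervention) x gap. A positive value shrinks the observed benefit; a negative value inflates it.

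| Usual care lost | Intervention lost | Gap (SD) | Bias (SD) | Bias / 0.5 SD target |
|---|---|---|---|---|
| 5% | 8% | 1.0 | (0.05 - 0.08) x 1.0 = -0.03 | -6% |
| 5% | 3% | 0.5 | (0.05 - 0.03) x 0.5 = +0.01 | +2% |
| 15% | 8% | 1.0 | (0.15 - 0.08) x 1.0 = +0.07 | +14% |
| 15% | 3% | 1.0 | (0.15 - 0.03) x 1.0 = +0.12 | +24% |

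The first and last rows are the extremes when the assumed ranges are fully crossed. With equal loss and equal gap in both arms the bias is zero. For scale, 15% of 80 is 12 usual-care participants who would all have to develop a condition, have it detected and lack approval, so the upper end is demanding.

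**4. What the planned analysis recovers.** The table describes a simple available-case comparison. The planned mixed model also uses BMI from baseline, 3 and 6 months, so it can absorb the part of the loss that earlier BMI predicts. It does not absorb what depends on the unseen later course. Standard multiple imputation rests on the same missing-at-random assumption, and standard hot deck on a similar one. Baseline carried forward is a single fixed assumption that gives no change to someone who gained weight.

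**The case against.** The strongest reply is that the rule says participants may continue, and that loss arises only when a PCP who had already approved participation declines or does not respond. A reader might infer that the rule breaks the intent-to-treat analysis, or that the analysis set is no longer everyone randomized. The article does not support either reading: no sentence removes anyone from the analysis or from the assigned arm, recorded BMI values are kept, and sensitivity analyses for missing outcomes are planned. This part of the objection stands.

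Three further points also stand.

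- **Sign.** It is tempting to conclude that losses concentrate in usual care and pull the result toward the null. The extra contact in SM and CM could equally raise detection there, and the assumed ranges include a negative bias.
- **The PCP's knowledge of arm.** The messages can be viewed; nothing shows that PCPs read them, can tell SM from CM, or let this affect approval.
- **Breadth of the trigger.** The sentence is a safety provision with a disease as its example. Whether it reaches exclusions aimed at contamination, such as joining another lifestyle program, is doubtful.

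The objection does not remove the wording itself. Assessments are expressly tied to approval, and the planned methods soften informative loss but cannot recover a value that was never measured.

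**Conclusion.** The concern holds in a limited form. The approval rule makes outcome assessment, and not only treatment, depend on a post-randomization event related to the outcome and on a third party's decision. The pregnancy clause ends assessment outright. Both sit badly with the stated intent-to-treat analysis and with the Retention section's effort to obtain final assessments from people who have stopped the intervention.

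The consequence is a weakened analysis, and its size cannot be fixed from the article. On the assumed rates and gaps, available-case bias lies between about -0.03 and +0.12 SD, or -6% to +24% of the 0.5 SD target. It vanishes if loss and gap are alike across arms, and the mixed model would be expected to reduce whatever part earlier BMI predicts. The case for acting rests on the loss being created by wording and cheap to avoid, not on a demonstrated large bias.

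**What to change.** Reconcile Participant Safety, Retention and Data Analysis as follows.

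1. Let the PCP-approval rule govern continuation of the intervention only. State that outcome assessments, at least weight, are still sought from all randomized participants unless they withdraw consent.
2. State explicitly how the pregnancy clause applies to outcome collection and how those participants' missing outcomes are handled in the analysis.
3. For anyone not seen at month 15, add the nearest clinic weight to the health-record extraction already planned at that point. Inclusion criterion 7 already asks participants to allow extraction of relevant record data. Use this weight in a sensitivity analysis only.

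The cost is a wording amendment and one extra extraction field. The downside is that clinic weights are less standardized than study weights, which is why they should not enter the primary analysis. The approval rule for the intervention itself is not questioned, and no clinical rule is proposed.

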**Data extracted from PAMF electronic databases**				
Current medical problems	X			X
Medications prescribed	X			X
Health care utilization	X			X
PCP characteristics	X			

^1^Questionnaire administered to participants in the SM and CM interventions only

Abbreviations: HDL-C, high-density lipoprotein cholesterol; LDL-C, low-density lipoprotein cholesterol; PCP, primary care provider.

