Additional secondary outcomes include generic and obesity-specific health-related quality of life and mental health. The 12-item Short Form Health Survey (SF-12) [31], a widely used quality of life instrument, is administered to evaluate changes in non-disease specific physical and mental health status. The Obesity-Related Problem Scale specifically measures the impact of obesity on psychosocial functioning. The eight-item scale has high internal reliability and sound test--retest reliability, correlates strongly with a wide range of theoretically related constructs, and is responsive to weight loss intervention [32]. The nine-item Patient Health Questionnaire (PHQ-9) refers to the previous two-week interval and consists of nine items of depression symptoms and one follow-up question on functional impairment [33]. The PHQ-9 is both a measure of depressive symptomatology and a tentative diagnostic instrument for the *Diagnostic and Statistical Manual of Mental Disorders*, 4^th ^edition (DSM-IV) depressive disorders [34]. The 21-item Depression Anxiety Stress Scale has high internal consistency and correlates strongly with other validated self-report measures of depression, anxiety, and stress [35].

Furthermore, changes in diagnoses, medication use and health care utilization will be assessed. With participant authorization, data are extracted from their EHRs at baseline and again at 15 months on current medical problems, current prescription medications, and health care contacts during the study (including outpatient visits, ER visits, hospitalizations, and phone/email consultations). Pharmacy dispensing data are currently available for patients with capitated insurance only (making up about 30% of the PAMF patient population). While the vast majority of health care of PAMF primary care patients, including specialist care, is received from PAMF, a significant proportion of medications prescribed are not obtained from the PAMF pharmacy. Also, PAMF patients may seek care outside the system. Therefore, additional data are obtained on medication and supplement use by recording information from the container and on health care outside PAMF by participant self-report.

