### Data Management

All study data are entered into computerized data files utilizing: 1) Microsoft Access for participant tracking and intervention data entry, 2) Vovici's survey software (Dulles, VA) for self-administered questionnaires and entry of clinical measurements, 3) Food Processor, v8.7 (ESHA Research, Oregon) for nutrient analysis based on three-day food records, and 4) a custom-designed web application for seven-day physical activity recall data entry. Research assistants (blinded to treatment assignment) will review participant responses on questionnaires with participants present, and skipped or incorrectly addressed items will be brought to the participant to correct. All of the data entry systems employ automatic, real-time range, logic, and missing value checks. Data sets will be cleaned, verified and archived, and then read into SAS (Enterprise Guide 4.1; SAS Institute, Cary, NC) data sets, which also are archived. One official copy of all the study data and a master data dictionary are maintained and updated regularly by the study data analyst. All analytic and tracking database files are stored in a secure network drive with daily backups. One copy of the backups is saved on-site and one off-site. Separate archival databases are permanently maintained. The data files can be shared by authorized study personnel both on-site and in remote locations via a secure virtual private network. Multiple levels of password protection are utilized to ensure data security.

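### Adverse-event records rest on questionnaires at months 3, 6 and 15; the planned 15-month record extraction should be added as a check for participants who never complete a later one

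*Protocol article*

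**What the plan says.** **Method.** Participant Safety states that "Surveillance for adverse events and relevant clinical events occurs by questionnaire at regularly scheduled intervals". The adverse events row of Table 2 marks months 3, 6 and 15. The route into the adverse event records is then given: "Positive responses trigger an adverse event record, which is reviewed by the study physician for seriousness, study relatedness, and expectedness within 72 hours".

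**Same in every arm.** The only arm restriction in Table 2 is a footnote on the technology-acceptance questionnaire: "Questionnaire administered to participants in the SM and CM interventions only". Data Management adds that "Research assistants (blinded to treatment assignment) will review participant responses on questionnaires with participants present".

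**Supplement.** Participant Safety continues: "Similar information reported by participants at other times (e.g., during intervention encounters) is duly noted and followed up with as needed".

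**Removal.** If a participant becomes pregnant, "she is excluded immediately from further participation in all study activities". Participants who develop another exclusionary condition "may continue with the interventions and follow-up assessments only after explicit approval of their PCP".

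**Record extraction.** Primary and Secondary Outcomes plans an extraction from the electronic health record, with authorization, at baseline and month 15. It covers medical problems, prescriptions and health care contacts, including emergency visits and hospital admissions. Its stated purpose is that "changes in diagnoses, medication use and health care utilization will be assessed". The article does not connect it with adverse-event surveillance.

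**The concern.** For participants who complete the questionnaires, ascertainment is symmetric and is reviewed by blinded staff. The weakness lies with those who stop completing them. Loss can be related to harm, since someone who dies or becomes too ill cannot fill in a form. The remaining route is a report made at another time, and the planned contacts that could prompt one differ by arm.

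The study could therefore hold chart evidence of an admission at month 15 while its adverse event records show nothing for that participant. What is at stake is the completeness of the serious-event counts, and how far those counts can be compared between arms.

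**Working it through.** **Inputs.** Target sample 240, randomized 1:1:1, so 80 per arm (Recruitment and Screening Process; Randomization and Blinding). Loss to follow-up of up to 20% (Sample Size). Treatment and follow-up of 15 months (Abstract). Adverse-event questionnaires at months 3, 6 and 15 (Table 2).

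**The plan's own figure.** The article gives no figure for adverse events. The 20% allowance comes from the power statement, which reproduces: 80 × 0.80 = 64 completers per arm, and a difference of 0.5 SD at two-sided α = 0.05 gives power of 0.801 by t-test (0.807 by normal approximation), against the stated value of about 80%.

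**Time after the last questionnaire.**

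- Total planned time: 240 × 15 = 3600 person-months.
- Participants lost at 20%: 240 × 0.20 = 48 (16 per arm if even). At an assumed 10%: 24.

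| Last questionnaire completed | Months after it | 20% loss (48) | 10% loss, assumed (24) |
|---|---|---|---|
| Month 6 | 15 − 6 = 9 | 48 × 9 = 432 (12%) | 24 × 9 = 216 (6%) |
| Month 3 | 15 − 3 = 12 | 48 × 12 = 576 (16%) | 24 × 12 = 288 (8%) |
| None | 15 | 48 × 15 = 720 (20%) | 24 × 15 = 360 (10%) |

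Each row treats all lost participants as having the same last questionnaire; a mixture falls between the rows.

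**Planned staff-initiated contacts for an engaged participant** (Intensive Treatment Phase; Maintenance Phase).

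- CM: 12 weekly sessions + at least 12 monthly messages = at least 24.
- SM: 1 orientation session, plus reminders to self-monitor every two weeks over 12 months, 52 / 2 = about 26. The dietitian answers messages but starts none in maintenance.
- Usual care: none described.

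These counts describe engaged participants, so they do not measure contact among those lost.

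**What the extraction could add.** The documents give no recovery rate. As an illustration only, suppose 20% are lost, event rates are equal in lost and retained participants, the questionnaire covers all events in the retained 80% and none in the lost, and the chart shows 30%, 50% or 80% of events in the lost. Coverage then rises from 80% to 0.80 + 0.20 × 0.30 = 86%, to 90%, or to 96%.

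**The case against.** **It is an article.** A journal article may leave the handling of reports to the full protocol, and nothing here is contradictory. That holds for one detail: whether a volunteered report becomes an adverse event record may be settled elsewhere, and no weight is placed on its absence. It does not dispose of the main point. The article names its surveillance method and schedule, and separately gives the extraction a different purpose.

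**The participants are not out of reach.** A reader might infer that the plan cannot reach anyone who misses a visit. The documents do not support this. Under Retention, assessment staff contact those who miss an assessment, with no arm restriction, and interventionists keep contacting those who discontinue unless they decline. Reports at other times are accepted, and a participant who returns may report earlier events. The gap is confined to those who never complete a later questionnaire and to those removed. Removal is automatic only for pregnancy; women planning a pregnancy are not enrolled, and the primary care physician is told at once. For other conditions, follow-up may continue if the physician approves.

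**Charts are not simply better.** They miss care outside the health system and events never brought to care, and at month 15 they come too late for the 72-hour review. This stands: extraction is an additional source, not a replacement for volunteered reports.

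**CM will look less safe.** A reader might infer this from the contact counts. With assumed capture of 50% to 90% by questionnaire, and 20% to 50% of the remainder through CM encounters, equal true rates would give an observed CM to usual-care ratio of 1.02 to 1.50. None of those capture rates is in the documents, so neither the size nor the direction of an imbalance is established.

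**Conclusion.** The point holds as a minor, inexpensive improvement. As written, serious events after the last completed questionnaire may be missing from the adverse event records of participants who never return or who are removed for pregnancy, although data already planned in every arm could show them.

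At the 20% loss allowed for, the time concerned is 432 to 720 of 3600 person-months (12% to 20%), depending on the last questionnaire completed. This rests on the power allowance being used up, which is an assumption about 15-month loss and not a forecast of safety coverage. Successful re-contact would lower it. Unobserved person-months are not missed events: the article gives no event rates, so the number missed and any difference between arms are unknown. Adverse events are not a primary or secondary outcome, and the BMI analysis is unaffected.

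**What to change.** In Participant Safety and in Primary and Secondary Outcomes, state that:

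1. Emergency visits, hospital admissions, major new diagnoses and deaths found in the 15-month extraction are checked against the adverse event records. Deaths are not among the extracted items listed and should be added.
2. The check covers all randomized participants whose authorization stands, including those lost or removed. Say explicitly that passive extraction continues after removal, since exclusion from all study activities could be read as ending it.
3. Unmatched events go to the existing study physician, masked to arm.
4. Serious events are reported by arm and by source (questionnaire, volunteered report, record). The between-arm comparison uses questionnaire plus record. Volunteered reports are kept and shown separately.

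**Cost.** Some extra physician review of data already planned; willingness to allow extraction is an entry condition in Table 1. Reported counts may rise. The check is retrospective, so the 72-hour review gains nothing, and care outside the health system remains self-reported.
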